#### Process evaluation

•The web evaluation questionnaire (WEQ) will contain questions about content, layout, the perceived effectiveness and usefulness of the website, as well as the question to give the website a motivated overall score from 0 to 10, based on their experiences and taking into account their own wishes and needs. The evaluation questionnaire has as goal to identify issues for further improvement of “Feel the ViBe”, to collect possible facilitators and barriers for implementation and to evaluate if the website meets the expectations of the target group. The WEQ is measured twelve weeks after getting access to Feel the ViBe, being t = 2 for the intervention group and t = 4 for the control group.

•“Use” is measured by the collection of quantitative data - being amongst others and duration, visited pages, and visitor numbers - and qualitative data - being forum and chat entries and questions asked to the experts – and is monitored on a continuous base [50,51].

•Demographic variables and data on other (health) care and support received will be collected. At t = 0, participants will also be asked to their expectations, needs and wishes for “Feel the ViBe”.

•After participants have finished all components of the intervention, including all questionnaires, they will be asked if they consent to take part in an interview to discuss in dept their experiences with the intervention.

All questionnaires are provided online and are mandatory to get access to other features. The IES, the SCL-90 and the “Sex-under-25” questionnaire have been administered online before in other studies. Both the general questionnaire and the WEQ have been developed for this trial. Comments and suggestions of test users were incorporated. All the questionnaires have been tested for usability and technical functionality. All responses are being captured automatically.

The primary outcome measures, being the IES and the SCL-90R subscales will be administered four times. This will give us the possibility to determine the optimal duration of the intervention. Participants receive a reminder in their personal menu and via a text message (Figure 1).

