## Methods/design

### Trial design

This study is a randomized controlled trial using the method of minimization, as described by Taves (1974), to randomize the participants in two parallel groups with a 1:1 allocation ratio, being an intervention group, having access to “Feel the ViBe” + usual care (UC), and a control group, having access to minimally enhanced usual care (mEUC) [40,41]. Subcategories for the process of minimization will be sex (male or female) and age (12–17 years old and 18–25 years old). The study is conducted in the Netherlands. This trial is registered in The Netherlands National Trial Register (NTR) and assigned the trial ID NTR3692.

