Questionnaires	Measure outcomes and need to be filled out before accessing the elements behind login. Questionnaires will be activated in the personal menu. Questionnaires can be filled out one-by-one. Whenever possible, adaptive questioning is being used to make the burden as low as possible. There is a maximum of 15 questions per page. All items need to be filled out to submit a questionnaire. Participants cannot review their answers.	Available after first login, re-activated after 6,12, 18 and 24 weeks. *Element will no longer be obligated after trial.*
Personal menu	Menu for the participants with overview to all the available elements, access to the participants profile, digital testament, research information and contact information.	Login needed
User profile	The profile contains information on the participant, being: full name, nickname, avatar, sex, age, contact details and contact person. Only the nickname is available for other participants. The participant can choose a theme for the lay-out.	Login needed
Digital testament	The digital testament is required to fill out and lets participants choose how their data must be handled if they stop their participation.	Login needed
Ask the expert	Option to ask questions by e-mail to several experts, including a general practitioner, a sexologist, a psychologist and an expert in the field of family violence. Participants can also contact the community manager for general questions and questions regarding regular healthcare services. Response is given within 72 hours. During the RCT, this is the only available element for participants in the control group.	Login needed & questionnaires finished
Forum	The forum is meant to stimulate peer support. The community manager moderates the forum and stimulates contact. She will not intervene in the conversations except in case of offensive or factually wrong comments.	Login needed & questionnaires finished
Chat	Every two weeks we will offer a chat session for the participants with a specific theme and supported by an expert. Every other week there will be an unguided chat.	Login needed & questionnaires finished
Information	Information will be offered to the participants. Depending on the age in the profile, participants have access to tailored information about partner violence, sexual health, reproductive health, relations and healthcare. Participants are encouraged to discuss topics on the forum.	Login needed & questionnaires finished

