Routine Outcome Measurement (ROM)	Directly after login and after logout a popup appears to the participant requesting to state their mood by means of smiley’s. The smiley is optionally visible in the profile as avatar.	Login needed
Facts & Figures	In a twelve-week cycle, participants receive a one-sentence fact of figure about family violence, sexual health, or reproductive health every day on their mobile or by e-mail.	Questionnaires finished

Overview of the elements of the internet-based self-support method “Feel the ViBe”, including restrictions for participants.

“Feel the ViBe” is to be used ad libitum. However, to stimulate participation, participants receive a fact or figure by email or text message every day (Table 1). Elements, such as the guided chat and “facts and figures”, are repeated every twelve weeks. Strictly spoken there is no hard endpoint to the intervention, because “Feel the ViBe” is meant to support participants as long as they need this. However, we decided to link measurements to this twelve week period (Figure 1). Some items are obligatory to fill out to gain access to other features, such as the questionnaires. Restrictions are given in Table 1. “Feel the ViBe” is monitored by a community manager who answers questions, guides the chat, moderates the forum and addresses possible safety issues with participants. To prevent bias, the Community Manager uses a protocol. Every action from the community manager not covered by the protocol will be registered, discussed with the supervising research team, and, if necessary, added to the protocol.

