**Figure 1 F1:**
[figure not shown]
**Flowchart randomization procedure, received care and data collection.** Abbreviations: mEUC = minimally enhanced usual care, UC = usual care.

The intervention group will receive immediate access to “Feel the ViBe” after registration. Considering ethical concerns of withholding an intervention with a possible positive effect on physical and mental health, the control group will be a waiting list condition receiving minimally Enhanced Usual Care (mEUC) for twelve weeks before getting access to the intervention. mEUC is in general defined as non-study care enhanced in minor ways to address methodological or ethical issues. For this RCT mEUC is defined as Usual Care and access to a restricted version of “Feel the ViBe” offering only access to the user profile, consent forms, digital testament, research information, questionnaires and the “ask the expert” function to ask questions in case of emergency. Questions asked by members of the control group will not be answered by the Community Manager, but by one of the members of the Research Team who is not actively involved in the intervention, being author [name]. If help is needed immediately, the participant will be referred to his/her GP (Figure 1).

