#### Primary outcome measure

•The Impact of Event Scale (IES) will be used to measure PTSD symptoms. The IES is a short set of 15 questions measuring the impact of events and the amount of distress associated with events. It comprises the subscales Intrusion (8 items, mean α = 0.86) and Avoidance (7 items, mean α = 0.82). The IES is measured at t = 0, t = 1, t = 2, t = 3 and t = 4 for both groups [44-46].

•The Depression and Anxiety subscales of the Symptom CheckList-90-R (SCL-90-R DEP and ANX) will be used to measure an improvement in symptoms of depression and anxiety. The SCL-90-R DEP and ANX subscales measure symptoms of depression and anxiety during the previous week on a five-point Likert scale. Both subscales showed good convergent and divergent validity, and high internal consistencies. The SCL-90-R is validated for participants of twelve years old and older. The depression subscale comprises 16 items (α = .90), the anxiety subscale comprises 10 items (α = .88). The SCL-90-R DEP and ANX subscales are measured at t = 0, t = 1, t = 2, t = 3 and t = 4 for both groups [47].

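### Repeated measurement cannot determine an optimal duration: no stopping time is assigned, and the comparison with delayed access is lost after week 12

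*Protocol article*

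**What the plan says.** The design statements come from several sections of the Protocol article.

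- **The claim** (Process evaluation): "The primary outcome measures, being the IES and the SCL-90R subscales will be administered four times", followed by "This will give us the possibility to determine the optimal duration of the intervention".
- **Arms** (Trial design): the plan is "to randomize the participants in two parallel groups with a 1:1 allocation ratio". The two arms are the intervention with usual care, and minimally enhanced usual care (mEUC).
- **Length and intensity of use** (Intervention): the method "is to be used ad libitum", and "Strictly spoken there is no hard endpoint to the intervention". Twelve weeks is the cycle after which content repeats and to which the measurements are tied. It is not a course length given to anyone.
- **Control condition** (Intervention, text below Figure 1): "the control group will be a waiting list condition receiving minimally Enhanced Usual Care (mEUC) for twelve weeks before getting access to the intervention".
- **Measurement times**: Table 1 describes the questionnaires as "Available after first login, re-activated after 6,12, 18 and 24 weeks". Under Primary outcome measure, "The IES is measured at t = 0, t = 1, t = 2, t = 3 and t = 4 for both groups"; the SCL-90-R subscales have the same time points.
- **Analysis** (Data analysis): ANOVA of the primary outcomes, between groups and within subjects. Duration appears neither there nor in the objectives.

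**The concern.** To determine an optimal duration, one must compare what happens when people have the intervention for different lengths of time, including what happens once it ends. Here everyone who has received access keeps it, and how much they use it is their own choice. Measuring more often shows how symptoms develop while access continues. It does not show what would follow if access ended at a given week.

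After week 12 the control group also has access. A change within either arm from then on can reflect the intervention, natural recovery, regression to the mean, or selective loss of participants, and the article itself expects high attrition. If scores level off at some week, this could be taken as the point at which the intervention has done its work, although randomisation would not support that conclusion.

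**Working it through.** **1. The stated count.** Process evaluation gives 4 administrations. Table 1 gives first login plus weeks 6, 12, 18 and 24, so 1 + 4 = 5. Primary outcome measure lists t = 0 to t = 4, also 5. The figure of 4 matches only the post-baseline waves.

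**2. Weeks of available access.** At week w the intervention arm has had w weeks and the control arm max(0, w − 12).

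| Wave | Week | Intervention | Control |
|---|---|---|---|
| t = 0 | 0 | 0 | 0 |
| t = 1 | 6 | 6 | 0 |
| t = 2 | 12 | 12 | 0 |
| t = 3 | 18 | 18 | 6 |
| t = 4 | 24 | 24 | 12 |

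Two of the four follow-up waves compare access with none. Here none means mEUC, which includes the restricted site.

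**3. What each arm difference estimates.** Let f(a) be the mean effect, against mEUC, of a weeks of access from registration. Let g(a) be the same for access that starts 12 weeks later. Let D(w) be the arm difference at week w.

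- D(6) = f(6) and D(12) = f(12). Randomisation handles natural recovery and regression to the mean here.
- D(18) = f(18) − g(6) and D(24) = f(24) − g(12).

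The last two mix length of access with delay. They yield f(18) and f(24) only if g = f, that is, if the effect depends solely on time since access. Then f(18) = D(18) + D(6) and f(24) = D(24) + D(12).

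**4. Precision of that route.** Inputs: 50 per group and 80% power from Sample size. Assumptions: two-sided 5% test (the article gives 95% confidence but not the sidedness), no loss, outcomes in SD units, and correlation ρ between the two arm differences of 0 to 0.7.

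- Single difference: SE = √(2/50) = 0.20. Detectable d = (1.960 + 0.842) × 0.20 = 0.56.
- Sum of two differences: SE = 0.20 × √(2 + 2ρ), which is 0.28 at ρ = 0 and 0.37 at ρ = 0.7. Detectable d = 0.79 to 1.03.
- With 26 per group analysed (an illustrative assumption): SE of one difference = √(2/26) = 0.277, and detectable d for the sum = 1.10 to 1.43.

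Even without loss, the bridged 24-week effect would have to exceed 0.7, the smallest effect cited in Sample size, to be found with 80% power. In fairness, if g = f, the gain from 12 to 24 weeks is f(24) − f(12) = D(24) alone, with detectable d 0.56. To conclude that nothing is gained after week 12, one would rely on a 95% interval of ± 1.96 × 0.20 = ± 0.39 SD. Precision is therefore a secondary limit; the assumption g = f comes first.

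**5. Stopping.** Every f(a) above is measured while access continues. An optimal duration needs outcomes at a common later time after different assigned ends of access. No arm has an assigned end, so no analysis of these data supplies that contrast by randomisation.

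**The case against.** The strongest defence is that the design carries more information on duration than it first appears to, and that the sentence promises little.

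- A reader might infer that the control arm ends at week 12. It does not. Only the mEUC condition ends; the control group is measured through t = 4.
- A reader might infer that weeks 18 and 24 hold no controlled information. That is too strong. Randomisation fixes available access at 18 against 6 weeks and at 24 against 12. What is lost is the comparator without access, not randomised comparison as such.
- A reader might take the late scores as maintenance. For controls they are the first 6 and 12 weeks of access, and for the intervention group they are continued access.
- At weeks 6 and 12 the control arm does separate effect from natural course, so the effect after 6 weeks can be set against that after 12.
- The sentence speaks only of a possibility and sits under Process evaluation. No objective, sample-size figure or planned test depends on it, and the article does not say that a duration result will be reported as a trial finding.

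All of this stands, and it narrows the point. It does not rescue the claim: the staggered start confounds length of access with delay, and none of these contrasts involves stopping. Nor is this a matter of detail left to a fuller plan, because no analysis can create an assigned stopping time.

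The count of four can be read as the four re-activations. As written, it still disagrees with the other two sections.

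**Conclusion.** The concern holds as a minor point of wording. The design can show how early an effect appears (weeks 6 and 12, randomised against mEUC) and can describe the course to week 24. It cannot determine an optimal duration. Two of four follow-up waves have a comparator without access, and none has an assigned stopping time. The other two waves offer a randomised difference in available access that is confounded with a 12-week delay. This difference gives effects beyond 12 weeks only if the effect depends solely on time since access, and then only under continued access.

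The detectable effects above rest on 50 per group without loss, a two-sided test and an assumed correlation; the conclusion does not depend on them. The primary comparison is unaffected.

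The mismatch between four and five administrations is real but slight, since Table 1 and Primary outcome measure agree on the schedule.

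**What to change.** In Process evaluation, replace the sentence on optimal duration with a statement to this effect:

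- arm differences at 6 and 12 weeks describe how early an effect appears;
- scores at 18 and 24 weeks reflect continued access in the intervention group and the first 6 and 12 weeks of access in the control group;
- these later scores are exploratory descriptions of the time course and cannot establish an optimal duration.

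If effects beyond 12 weeks are to be derived from the staggered start, state the assumption that they depend only on time since access.

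In the same paragraph, reconcile the four administrations with the five time points in Table 1 and Primary outcome measure, for example as baseline plus four follow-ups.

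The cost is wording only. Data collection, sample size and participant burden stay the same, and one secondary claim is given up.

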### Sample size

For the calculation of de sample size of the RCT, we searched for studies investigating internet-based methods with the Impact of Event Scale (IES) as a primary outcome measurement [52-55]. We set the confidence interval to 95% and the power to 80%. We calculated the minimal sample sizes using the Cohen’s *d* effect sizes found in these studies. In general, an effect of 0.5 is considered to be a large effect. In the four selected studies, the effect size ranged from 0.7 (leading to 26 participants needed) to 2.0 (4 participants needed), with a mean of 11 and a median of 9 participants needed for each group. Considering the relatively high effect sizes found in these studies and because both the subject of the study and the age of the participants can lead to high drop-out, as seen before in a group of sexually abused adolescents, we aim to include 50 participants for each group at t = 0 [53].

### Randomization

Randomized trials with children and adolescents are controversial. The subject of our study enhances this even more. However to measure the effectiveness of an intervention, a randomized controlled trial is preferred above pre- post-test designs. Participants registering themselves online will be randomized to the intervention or the control group using the method of Minimization, as described by Taves (1974) [40,41]. Subcategories will be sex (male or female) and age (12–17 years old and 18–25 years old). This method minimizes the difference between the intervention and the control group. The allocation is carried out with help of a computer program by a research assistant.

Due to the nature of the study, participants cannot be blinded. Because of the nature of the overall study, containing both quantitative and qualitative parts, blinding of the investigators is difficult because the researchers need to know the group of the participant to be able to perform qualitative analysis and to follow each participant individually for the process evaluation. However questionnaires will be collected automatically during the trial in a SPSS file and delivered anonymized to the researchers.

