#### Recruitment and informed consent

Participants will be recruited both offline and online, by posters and flyers of the website “Feel the ViBe” spread amongst stakeholders in the field, general websites and social media to reach as many participants as possible. In this target group, internet literacy is assumed.

According to the principles of Dutch law, for participants age 12 to 16 years old, both parents (or guardians) must consent in addition to the minor him/herself. However, in cases of family violence, informing the abusive partner can be potentially dangerous, for both the abused parent and the adolescent exposed to the violence, and safety cannot be ensured. Therefore, in these cases we ask informed consent from the abused parent, being the mother in most cases, only.

Participants register themselves by sending an email to the community manager through the contact form online. In this early phase, inquiring participants about the type and severity of the violence would enlarge the threshold for participation. We therefore choose to consider every potential participant eligible as target group. If participants have read the patient information letter, available on the homepage, and have no further questions, they are eligible to participate and will receive a login name and password. On their first login, participants have to give informed consent electronically. If applicable, participants are requested to provide contact information of their parent(s), who then receive a unique code and a link to give consent as well.

The intervention is internet-based without face-to-face components. This means that participants are quasi-anonymous for each other. Having multiple identities is being prevented by making the registration a manual process, including a IP-address check and e-mail contact, and the informed consent process.

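### Allocation appears to come at registration, before consent and the baseline questionnaires, and the minimisation states no random element, so most assignments can be foreseen by anyone holding the running totals

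*Protocol article*

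**What the plan says.** **Method and operator.** The Randomization section states: "Participants registering themselves online will be randomized to the intervention or the control group using the method of Minimization, as described by Taves (1974". The factors are sex and age group (12–17 and 18–25). On who does it: "The allocation is carried out with help of a computer program by a research assistant". No random element is mentioned, and the same section says that participants cannot be blinded.

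**Registration and access.** Under Recruitment and informed consent: "Participants register themselves by sending an email to the community manager through the contact form online". A login name and password follow. In the Intervention section, below Figure 1: "The intervention group will receive immediate access to" the website, with registration given as the starting point.

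**Consent.** Under Recruitment and informed consent: "On their first login, participants have to give informed consent electronically". Where parental consent applies, "participants are requested to provide contact information of their parent(s), who then receive a unique code and a link to give consent as well".

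**Baseline.** Table 1 describes the questionnaires as "Available after first login, re-activated after 6,12, 18 and 24 weeks". They "Measure outcomes and need to be filled out before accessing the elements behind login".

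**The concern.** Two separate matters arise.

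The first is order. If people are allocated when they register, everything that can remove them before baseline happens after allocation: not logging in, not consenting, a parent not consenting, or not finishing the questionnaires. If they also know their arm by then, someone on the waiting list may leave, or may answer the t = 0 IES and SCL-90-R items differently from someone about to get access. All outcomes are self-assessed (Settings), and t = 0 anchors the pre-post comparison (Data analysis). The target of 50 per group is counted at t = 0 (Sample size), so a count at that point would not show who had been allocated and lost before it.

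The second is predictability, which does not depend on the order. Minimisation as cited is deterministic except at ties. With only two binary factors, the running totals settle most assignments before they are made, and a member of staff runs the procedure.

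**Working it through.** **Step 1: order of events.** There is no figure in the plan to reproduce here, so the statements are set side by side.

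| Event | When | Where stated |
|---|---|---|
| Registration by e-mail | start | Recruitment and informed consent |
| Randomisation | tied to those registering; no other time given | Randomization |
| Intervention access | from registration | Intervention, below Figure 1 |
| Participant consent | first login | Recruitment and informed consent |
| Parental consent (under 16) | requested at or after first login | Recruitment and informed consent; Table 1 |
| t = 0 questionnaires | after first login | Table 1 |

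The restricted site that defines the control condition is also said to contain the consent forms and questionnaires (Intervention). This fits people already being in an arm when they meet them. Nothing in the text places allocation after consent or t = 0.

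**Step 2: predictability.** Inputs from the article are two factors with two levels each, 1:1 allocation and N = 100 (50 per group). Assumptions are equal factor weights, ties settled by a fair coin, one sex making up 50% to 90% of entrants and one age group 30% to 50%.

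For a newcomer of sex s and age group a, the total for each arm is

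S(arm) = n(arm, sex s) + n(arm, age a).

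The newcomer goes to the arm with the smaller S. For example, suppose the first entrant, a girl in the younger group, goes to arm A. A young woman in the older group comes next: S(A) = 1 + 0 = 1 and S(B) = 0, so B is certain.

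An observer who knows the earlier allocations and the newcomer's sex and age names the favoured arm, and guesses at ties:

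correct share = f × p + (1 − f) × 0.5,

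where f is the share of allocations with a favoured arm and p is the probability of assigning that arm. Results are from 1,000 simulated trials per setting, with 50% in each sex and age group:

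| p | f | Correct guesses | Mean difference in arm size |
|---|---|---|---|
| 1.0 (as cited) | 0.721 | 0.721 + 0.279 × 0.5 = 0.86 | 0.29 |
| 0.8 | 0.793 | 0.793 × 0.8 + 0.207 × 0.5 = 0.74 | 1.00 |
| 0.7 | 0.841 | 0.841 × 0.7 + 0.159 × 0.5 = 0.67 | 1.73 |

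The assumed shares hardly matter. Across the ranges above, f at p = 1 runs from 0.720 to 0.727 and correct guesses from 0.860 to 0.863. At p = 0.8, correct guesses run from 0.738 to 0.740 and the mean difference in arm size from 0.95 to 1.03.

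**Step 3: early loss.** Its effect on the treatment comparison cannot be computed. The article gives no rate of loss between registration and t = 0, overall or by arm.

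**The case against.** The strongest case is that the order is nowhere stated. The sentence on randomisation can be read as saying who is randomised, not when. Immediate access after registration cannot be literal, because consent and questionnaires must come before the content opens, and the phrase may only contrast with the control group's twelve-week wait. One sentence in the recruitment section can be read as counting consent within the manual registration process. Sex and age, which minimisation needs, are listed in a profile that requires login. Figure 1 charts the randomisation procedure and may settle the matter. All of this stands, and it makes the point on order conditional. It does not reverse it: the profile is also part of the control group's restricted site, so it does not show that allocation waits for consent or t = 0.

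A reader might go further and infer that the baseline is unblinded and that early losses do differ by arm. The document does not support this. It says participants cannot be blinded but not when they learn their arm, and both groups meet the same questionnaires before any content. These are risks created by the apparent order, not documented facts.

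A reader might also infer from the 86% that selection bias is present. That does not follow either. Every applicant is treated as eligible, people register themselves, registration goes to the community manager while a research assistant allocates by computer program, and nothing says that anyone views the totals. Little room is left for steering. What remains is that registration is a manual process with e-mail contact, and the article does not say the totals are kept from whoever handles it.

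Finally, minimisation without a random element is a recognised method, and a condensed article may leave program settings and concealment to the full protocol. Their absence alone is therefore not the criticism. The point rests on the method the article names, who runs it, and the order its wording implies.

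**Conclusion.** The concern holds in a conditional form. The wording makes allocation at registration, before consent and t = 0, the most natural reading, subject to Figure 1. On that reading, baseline answers may be given with the arm known and early losses may be arm-dependent, with unknown size and direction.

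Independently of the order, the cited method leaves about 72% of allocations determined and about 86% guessable to someone with the running totals and the newcomer's sex and age. These figures rest on equal weights, coin-settled ties and the assumed sex and age shares, to which they are insensitive. They measure guessability, not bias in an outcome. Neither matter changes the sample size.

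**What to change.** 1. Allocate, and show the arm to the participant, only when participant consent, any parental consent and all t = 0 questionnaires are complete. Table 1 already makes access to content depend on these steps, so the same check can trigger allocation automatically.
2. Assign the minimising arm with probability 0.8 instead of 1.
3. State the order of registration, consent, baseline, allocation and disclosure in the Randomization section, and align the sentence on access in the Intervention section.
4. If Figure 1 already places allocation after t = 0, correct the wording of those two sections to match it and add only the random element.

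The cost is a small change to the website script and the allocation program, a mean difference in arm size of about one participant instead of 0.3, and participants learning their arm somewhat later. No additional participants are required by the design. Contact during the wait is unaffected: the Ethical and safety section already lets participants reach the community manager before the obligatory parts are finished.
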